**Intervention design:**

Group A:

- The carefully monitored physiotherapy program will include active exercises of wrist and hand at 34°C in a whirlpool.
- After that joint mobilization will be performed to the radiocarpal joint. Subjects will undergo grade I or II mobilization of Maitland approach during the first 2 weeks with a dosage of 1cps (cycle per second) for 1 minute.
- In the following 4 weeks, the sustained mobilization of Grade III Maitland approach in anteroposterior and posteroanterior directions will be done with the stabilization of distal radius in neutral position.
- The end range of motion will be attained and the treatment will be progressed with mobilization Grade IV technique.
- Strengthening technique will include exercises with theraband. This treatment will be performed for 60 mins per day for 5 days a week for 6 weeks.

Group B: Those subjects in experimental group with the Leap motion control will be asked to actively move their fingers from initial resting position and execute maximally the following five movements with their wrist and hand: fingers flexion and extension, flexion and extension of the thumb, wrist radial and ulnar deviation, forearm pronation and supination and wrist flexion and extension (Fernández-González et al., 2019) for 30 minutes regularly. Rehabilitation games include-

1. Rhythm game: This game is aimed at helping patients perform flexion exercises for wrist joint. The buttons fall from above as music plays in the background, and must be pushed at the right time by the player.
2. Flappy Bird Clone: It is designed for wrist flexion and extension both in which the player is asked to control a bird flying over a series of tubes before the track ends.
3. Skiing Game: It requires wrist movement i.e. either extension or flexion and wrist radial or ulnar deviation. A skier who comes down a slalom track is guided by the player and must cross the gates (Corona et al., 2018).

**Outcome measures:**

Primary outcome measure:

1. Disabilities of the Arm, Shoulder, and Hand Outcome Questionnaire (DASH): It is a 30- item questionnaire that evaluates the patient’s ability to perform upper extremity activities for functionality.
2. Universal goniometer for ROM: Active flexion and extension, radial deviation, ulnar deviation, pronation and supination of the wrist will be measured by a goniometer. Participants will be assessed to expose their arms in a seated position and to remove any accessories (Tremayne et al., 2002).

Secondary outcome measure:

1. Grip strength : To check grip strength a Jamar dynamometer will be used. The participants would be tested in sitting position with the arm and shoulder in neutral position and elbow in 90 degrees of flexion, and neutral forearm (Tremayne et al., 2002). Then, subjects will be asked with all their strength to make tight fists to maintain that position for 4 seconds and then rest for 30 seconds. First, the unaffected side will be tested and then affected side will be tested. The maximum value obtained from 3 trials will be recorded.
2. VAS: The visual analogue scale is a measurement scale for pain, consisting straight line of 10 cm, the left edge shows “no pain” and the right edge shows the “worst pain”. The subjects will be asked to draw a straight line illustrating the severity of the pain felt during the assessment.

**Follow up:** All patients will be followed up at 6 weeks after rehabilitation and follow-up record forms will be completed. The time of the last rehabilitation training session will be recorded. Electronic follow-up rehabilitation records will be preserved. When patients drop out of the trial, the reasons for withdrawal will be recorded in detail. Comprehensive and supportive patient communication will be undertaken; patients lost to follow-up because of any reason will be got in touch as soon as possible and be followed up within 6 weeks. Data regarding patients withdrawal from the study.

**Data management:** Data from the trial will be kept in a secure, locked storage area with limited access for later review by a biostatistician, a researcher in charge.

**Power analysis:** With G*power analysis, the sample size in respective group is calculated to be 20 patients with 95% confidence interval, power of 0.95 and effect size of 0.8. Therefore 20 patients in both groups have to complete 6 weeks of follow-up to have adequate statistical power.

**Statistical analysis:** The SPSS latest version will be used to perform statistical analysis. To compare the group effect, two-way repeated measures ANOVA (analysis of variance) will be used. When ANOVA reveals a significant difference, student’s t test will be used to compare the changes within the group. Statistical significance is determined by a two-sided p value of less than 0.05. Mann-Whitney U, t-test or Fisher’s exact test will be used for comparing Groups at baseline and for comparing the primary and secondary outcomes between the groups at 6 weeks.

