**Hypothesis:**

- **Null hypothesis:** There is no significant effect of Leap motion tracking device in rehabilitation of distal radial fracture.
- **Alternate hypothesis:** There is significant effect of Leap motion tracking device in rehabilitation of distal radial fracture than conventional physiotherapy, either equal or superseding.

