**Perform post treatment assessment**

**Statistical Analysis**

**Participants:**

Inclusion criteria are as follows:

1. Age 18-50 years, who have been referred from the Dept. of Orthopaedic.
2. Patients must be diagnosed with an A3 extraarticular multi-fragmentary distal radial fracture type and treated conservatively with plaster cast immobilization and closed reduction.
3. Participants must accept and sign the Informed consent.
4. No previous history of wrist/ hand fracture, history of inflammatory arthritis, or any possible upper limb fracture.
5. Patients who are able to comprehend (Lyngcoln et al., 2005).

Exclusion criteria are as follows:

1. Participants who were treated for DRF reduction and/or fixation with some form of surgical intervention (e.g. external fixation, volar plate, and Kirschner wires).
2. Patients with Mini-Mental score less than 26 points on the examination.
3. After the removal of the immobilization, patients with immediate complications like malunion or non-union.
4. Patients with past trauma either in arms or hands that had impaired function.
5. Patients with inflammatory or non-inflammatory diseases and neurological disorder were excluded.

**Sample size consideration:** This is an experimental study with two-group design that examines the effect of leap motion control in distal radial fracture rehabilitation. Analysis of previous power using G*Power is used to determine the same size (Engel et al., 2019). 40 participants will be enrolled to the control group or experimental group and will be allocated accordingly (Maciel et al., 2005). The G*Power analysis followed the following terms for calculation of sample size which is graphical represented in figure 2.

**t tests** - Means: Difference between two independent means (two groups)

**Analysis:** A priori: Compute required sample size

**Input:** Tail(s) = One

Effect size d = 0.8

α err prob = 0.2

Power (1-β err prob) = 0.95

Allocation ratio N2/N1 = 1

**Output:** Non-centrality parameter δ = 2.5298221

Critical t = 0.8511828

Df = 38

Sample size group 1 = 20

Sample size group 2 = 20

Total sample size = 40

Actual power = 0.9531573

**Figure 2:** The calculation of sample size using G*Power analysis

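### Two primary outcome measures, one of them range of motion in six movements with no summary, are compared at an unadjusted 0.05 with no rule for what counts as success

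*Protocol*

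**What the plan says.** Under Outcome measures, the Protocol numbers two primary outcome measures. The first is "Disabilities of the Arm, Shoulder, and Hand Outcome Questionnaire (DASH"). The second is ROM by universal goniometer: "Active flexion and extension, radial deviation, ulnar deviation, pronation and supination of the wrist will be measured by a goniometer". Grip strength and pain on a visual analogue scale are secondary. No ROM total, average or lead movement is defined.

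The Statistical analysis paragraph sets one threshold: "Statistical significance is determined by a two-sided p value of less than 0.05". It plans tests for "comparing the primary and secondary outcomes between the groups at 6 weeks", and also states: "To compare the group effect, two-way repeated measures ANOVA (analysis of variance) will be used". It gives no alpha split, no order of testing and no multiplicity adjustment.

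The alternative hypothesis is global and names no endpoint: "There is significant effect of Leap motion tracking device in rehabilitation of distal radial fracture than conventional physiotherapy, either equal or superseding".

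The sample size calculation is for a single t test with d = 0.8, one-tailed, "α err prob = 0.2", power 0.95 and 20 per group. Neither it nor the later Power analysis paragraph says which outcome the effect size refers to.

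**The concern.** With more than one primary outcome, a protocol has to say what a positive trial is. If one significant primary is enough, each further test at 0.05 raises the chance of a false claim. If all must be significant, the false-positive rate is held but power falls. This Protocol does not choose, and it leaves open how many primary comparisons there are, because ROM could be analysed movement by movement, as arcs or as a total.

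The aim is comparative efficacy, and the Implication paragraph looks ahead to regular use of the device. In a trial of 40 people, a headline claim could rest on whichever primary measure happened to reach 0.05, chosen after the results were seen.

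**Working it through.** **Inputs from the Protocol.** Two-sided alpha 0.05 (Statistical analysis); 20 per group, d = 0.8, one-tailed alpha 0.2, power 0.95 (Sample size consideration); DASH plus six movements (Outcome measures). The Protocol gives no correlations between outcomes, so those below are assumptions.

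**1. The Protocol's own figure.** The noncentrality is 0.8 × √(20/2) = 2.5298, with 38 degrees of freedom. At one-sided alpha 0.2 the critical t is 0.8512 and power is 0.9532. All three match the printed output. The calculation is for one test on one unnamed variable.

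**2. How many primary comparisons?** By the Protocol's numbering there are two, if ROM becomes one measure. With each movement tested separately there are 1 + 6 = 7. If flexion and extension are taken as one arc there are six.

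**3. Chance of at least one false-positive primary, any-one rule, independent endpoints.** The formula is 1 − 0.95^k.

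- k = 2: 1 − 0.95² = 9.75%
- k = 6: 1 − 0.95⁶ = 26.5%
- k = 7: 1 − 0.95⁷ = 30.2%

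For differences favouring the device only, the formula is 1 − 0.975^k: 4.9% for k = 2 and 16.2% for k = 7. A single test gives 2.5%.

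**4. Correlated endpoints.** This was simulated with no true effect, 20 per group, two-sided t tests at 0.05, equal correlation between endpoints and 20,000 runs per setting.

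| Assumed correlation | 2 endpoints, either direction | 2 endpoints, favouring device | 7 endpoints, either direction | 7 endpoints, favouring device |
|---|---|---|---|---|
| 0 | 9.7% | 4.7% | 29.8% | 16.0% |
| 0.3 | 9.6% | 4.9% | 27.0% | 13.6% |
| 0.5 | 9.0% | 4.6% | 23.2% | 11.6% |
| 0.7 | 8.1% | 4.0% | 18.0% | 9.1% |
| 0.9 | 7.1% | 3.5% | 11.3% | 5.7% |

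The zero-correlation row agrees with the exact values in step 3 within simulation error. A repeat with 200,000 runs changed no entry by more than about half a percentage point. Letting DASH correlate less with ROM (0.3) than the movements do with each other (0.5) gives 23.7% for seven endpoints in either direction.

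**5. Power if the gap is closed.** The noncentrality stays at 2.5298.

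| Alpha (two-sided) | Critical t | Power with 20 per group | Per group for 95% power |
|---|---|---|---|
| 0.05 (one primary) | 2.0244 | 69.3% | 42 |
| 0.025 (first Holm step, two primaries) | 2.3337 | 58.1% | 49 |

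**The case against.** A reader might infer that the trial has seven primaries each tested at 0.05, and that its chance of a false primary success is therefore 20–30%. The Protocol does not support that as a statement of fact, for three reasons.

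- It numbers two primary measures and says only that the six movements will be measured. Separate testing is an inference from the absence of a summary.
- It nowhere says that any one significant result is enough. If all were required there would be no inflation.
- The 20–30% range needs correlations of at most about 0.6, and it counts false differences in either direction, including those against the device. Success for the device is about half as frequent.

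It is also fair to say that adjustment methods are often left to a SAP, and that nothing but list order ranks DASH above ROM; the Objectives list ROM and function separately.

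These points narrow the size but do not close the gap. The choice of primary outcome, and of the outcome that the sample size serves, belongs in a protocol. This one has a statistical section that sets a flat 0.05 over more than one primary. Under an any-one rule, even the mildest case considered, two endpoints correlated at 0.9, gives about 7% rather than 5%. Under an all-must-succeed rule, the sample size makes no allowance for the loss of power.

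**Conclusion.** The point holds in this form: there are two primary outcome measures, the ROM measure is undefined as an endpoint, and nothing says how the primary results combine into a conclusion. As written, the plan does not guarantee the 5% error rate for a primary claim.

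The size depends on three things that the Protocol leaves open: the number of ROM comparisons, the correlation between outcomes, and whether one significant result is enough. Under an any-one rule, with assumed correlations from 0.9 to 0, the chance of a false-positive primary difference in either direction is about 7–10% with two endpoints and about 11–30% with seven. For differences favouring the device it is about 4–5% and 6–16%, against 2.5%. These figures do not count the repeated measures ANOVA or the open choice between the t test and Mann-Whitney, which add further opportunities.

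Confidence is high in the gap itself. It is lower in any single figure within the ranges.

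**What to change.** Before the data are analysed:

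1. Name one primary outcome. DASH is listed first and is a natural choice, though not the only defensible one. Test it at two-sided 0.05.
2. State one time point for it. The Follow up paragraph places follow-up six weeks after rehabilitation, whereas the Statistical analysis paragraph compares groups at 6 weeks and the flow chart shows assessment after the 6-week intervention. These must be reconciled first.
3. Report the ROM movements as secondary, with 95% confidence intervals and a statement that they are not controlled for multiplicity.
4. Alternatively, keep DASH and one predefined ROM measure (a named movement or a defined summary) as two primaries, with Holm's procedure.

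**Cost.** This is more than a change of wording. ROM loses primary status, or the alpha is shared. The power statement must name its endpoint and be restated: with 20 per group and d = 0.8, power is 69% at two-sided 0.05, and 58% at the 0.025 of the first Holm step. The shortfall from 0.95 to 69% is not caused by the fix. It comes from the one-sided alpha of 0.2 in the calculation, a separate defect that naming the endpoint brings into view. The Protocol also gives no DASH standard deviation or target difference to support d = 0.8, so that basis would have to be supplied.

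### Grip is tested on both hands, but the analysed quantity is undefined and no planned test uses a baseline covariate, so precision on the only strength outcome is probably lost

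*Protocol*

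**What the plan says.** Grip strength by Jamar dynamometer is the first secondary outcome in the protocol's Outcome measures section. It is the only strength measure, so it alone serves objective 3 (muscle strength).

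- **Measurement.** Both hands are tested: "First, the unaffected side will be tested and then affected side will be tested". Then: "The maximum value obtained from 3 trials will be recorded". The text does not say whether the analysed quantity is the affected-side value, the side-to-side difference or the affected side as a percentage of the other. The unaffected-side value is given no role.
- **Analysis.** The Statistical analysis section has two parts that bear on this. The first is "To compare the group effect, two-way repeated measures ANOVA (analysis of variance) will be used". The second is a set of two-sample tests, chosen from Mann-Whitney U, t and Fisher's exact, used at baseline and again "for comparing the primary and secondary outcomes between the groups at 6 weeks". No covariate or normalisation is mentioned.
- **Level.** "Statistical significance is determined by a two-sided p value of less than 0.05".
- **Population and size.** Eligibility covers ages 18-50 with no restriction by sex, and 20 patients are planned per group.

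**The concern.** Normal grip strength can be expected to vary widely across adults of both sexes aged 18-50. That variation has nothing to do with treatment, but it enters the spread of 6-week affected-side grip and so widens the confidence interval for the group difference. Grip of the unaffected hand at baseline is a direct pre-treatment measure of it, and the protocol already collects it. Affected-side grip just after immobilisation plausibly also reflects pain and disuse, so the two baseline values need not carry the same information.

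The protocol itself names the 6-week tests, and none of them can use either baseline value as a covariate. With 20 per arm, a real difference in strength could be missed for want of precision that the trial has already paid for. Leaving the grip quantity open adds a second, smaller problem: it could be chosen after the data are seen.

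**Working it through.** **Inputs from the protocol.** n = 20 per group, d = 0.8 (Sample size consideration; not tied to any outcome), two-sided 0.05 (Statistical analysis).

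**Inputs assumed.** All correlations, since the documents give none. r1 is affected-side baseline with 6-week affected-side grip, r2 is unaffected-side baseline with 6-week affected-side grip, and r12 is between the two baselines. d is taken on the scale of the unadjusted SD.

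**Step 1: reproduce the plan's figure.** Noncentrality = 0.8 × √(20/2) = 2.5298, with 38 df. The sample-size entries are "Input: Tail(s) = One" and "α err prob = 0.2". They give critical t = 0.8512 and power 0.9532, as stated.

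**Step 2: the same trial at the analysis level.** At two-sided 0.05 with 38 df the critical t is 2.0244 and power is **0.69**. This is the reference for an unadjusted t test on 6-week grip.

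**Step 3: what the repeated measures ANOVA recovers.** With one baseline and one post-treatment assessment, as in the flow chart, its group-by-time test equals a t test on change. With equal SDs, the variance of change is 2(1 − r1) times the raw variance. ANCOVA on the affected-side baseline leaves 1 − r1² (37 df).

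| r1 | Change: variance | Change: power | ANCOVA: variance | ANCOVA: power |
|---|---|---|---|---|
| 0.3 | 1.40 | 0.55 | 0.91 | 0.73 |
| 0.5 | 1.00 | 0.69 | 0.75 | 0.81 |
| 0.7 | 0.60 | 0.89 | 0.51 | 0.93 |

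The ANOVA loses power at r1 = 0.3, is neutral at 0.5 and helps at 0.7. ANCOVA does better in all three rows.

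**Step 4: add the unaffected-side baseline.** R² = (r1² + r2² − 2·r1·r2·r12)/(1 − r12²). Residual variance is 1 − R², the standardised effect is 0.8/√(1 − R²), and df = 36. For 0.5/0.6/0.5: R² = (0.25 + 0.36 − 0.30)/0.75 = 0.413, so residual variance is 0.587. Against 0.75 for the affected-side baseline alone, that is a fall of 1 − 0.587/0.75 = 21.8%, equivalent to 0.75/0.587 = 1.28 times the patients.

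| r1/r2/r12 | Variance, affected baseline only | Variance, both | Further fall | Power, affected only | Power, both |
|---|---|---|---|---|---|
| 0.3/0.6/0.5 | 0.910 | 0.640 | 29.7% | 0.73 | 0.87 |
| 0.5/0.6/0.5 | 0.750 | 0.587 | 21.8% | 0.81 | 0.90 |
| 0.5/0.5/0.5 | 0.750 | 0.667 | 11.1% | 0.81 | 0.85 |
| 0.5/0.4/0.7 | 0.750 | 0.745 | 0.65% | 0.81 | 0.81 |
| 0.7/0.5/0.7 | 0.510 | 0.510 | 0.04% | 0.9318 | 0.9315 |

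The added gain vanishes when r2 is close to r1 × r12, as in the last row (0.5 against 0.49). It exceeds 30% if r2 is high and r12 low: at 0.5/0.7/0.3 the variance goes from 0.750 to 0.418, a fall of 44%. The table is therefore a set of illustrations and does not bound the gain.

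**The case against.** Four points can be made against this.

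- **A reader might infer that unaffected-side grip is excluded and that raw affected-side values are compared.** The protocol says neither. A t test on the affected side as a percentage of the unaffected side would fit the text. This stands, which is why the point is put as an undefined endpoint together with tests that take no covariate. Normalising would not reliably do the same job: with equal SDs, a side-to-side difference has variance 2(1 − r) times raw, which is 1.4 at r = 0.3.
- **Covariate choice for a secondary outcome is often left to the SAP, which is not shown.** That would answer a complaint about missing detail. Here the protocol itself names the between-group tests, so the choice is stated, and a better one is available from the same data.
- **The plan is not wholly unadjusted, because the repeated measures ANOVA uses each patient's own baseline.** This is correct, and the plan should not be described as ignoring baseline. But step 3 shows that the ANOVA does not reliably recover the loss, and it makes no stated use of the other hand.
- **The gain rests on assumed correlations and can be nil.** This also stands. A reader might infer that the unaffected hand always adds a worthwhile amount, and the last two rows of step 4 show otherwise. The unadjusted comparison is also valid and unbiased under randomisation.

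**Conclusion.** The point holds as an inexpensive improvement and does not identify a flaw in validity. The protocol collects grip on both hands, leaves the analysed quantity undefined, and names 6-week tests that cannot use either baseline as a covariate.

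At 20 per arm, d = 0.8 and two-sided 0.05, moving from the unadjusted t test to ANCOVA on affected-side baseline takes power from 0.69 to between 0.73 and 0.93 for r1 of 0.3 to 0.7. Adding the unaffected side gives, for example, 0.90 at 0.5/0.6/0.5. Its contribution beyond the affected-side baseline runs from about zero to about 30% of residual variance in the cases tabulated.

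These figures assume the correlations shown, a d that the protocol does not link to grip, and all 40 patients assessed. The outcome is secondary.

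**What to change.** In Outcome measures, define the grip endpoint as affected-side grip at 6 weeks. In Statistical analysis, state that groups are compared on it by ANCOVA with two covariates, baseline affected-side grip and baseline unaffected-side grip, and that the adjusted difference is reported with a 95% CI.

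Use only the baseline unaffected-side value, which the flow chart places before allocation. A 6-week value is measured after randomisation and should not be a covariate. Enter the unaffected side as a covariate, not as the denominator of a ratio.

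The cost is about one sentence and two degrees of freedom against the planned t test (38 to 36). It should need no new measurement, provided that both hands are tested at the baseline assessment. The protocol implies this but does not list measurements by visit, so the same edit should confirm it.

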**Material and Methodology:**

**Study design:** This interventional comparative study will be carried out in the HumEn Research Lab of Ravi Nair Physiotherapy College, Sawangi (Meghe), Wardha, after approval from Institutional Ethics Committee of Datta Meghe Institute of Medical Sciences, Deemed to be University. Before inclusion, all the participants will be informed regarding the aim and procedure of research. Those participants who will meet the inclusion criteria must give the written informed consent. In an experimental study, those participants (N= 40) diagnosed with distal radial fracture will be enrolled for 6 weeks protocol. The participants will be randomly assigned in a 1:1 ratio, a 6-week therapy with leap motion tracking device and a 6-week traditional therapy. Figure 1 shows the flow chart of the study.

**Recruit Subjects(N=40**)

Subjects will be screened by inclusion and exclusion criteria, informed consent & medical history will be obtained from subjects

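### The number of patients who must complete follow-up equals the number enrolled, so the stated 0.95 power has no margin for loss and should be restated at the number expected to be analysed

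*Protocol*

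**What the plan says.** The sample size calculation in the protocol (Sample size consideration) is a two-sample t test with "Effect size d = 0.8", "α err prob = 0.2" one-tailed, "Power (1-β err prob) = 0.95" and "Allocation ratio N2/N1 = 1". Its output is 20 per group, 40 in total, with an actual power of 0.9531573.

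The Study design paragraph sets enrolment at the same figure: "those participants (N= 40) diagnosed with distal radial fracture will be enrolled for 6 weeks protocol". The flow chart splits this into 20 control and 20 experimental subjects.

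The Power analysis paragraph then states: "Therefore 20 patients in both groups have to complete 6 weeks of follow-up to have adequate statistical power".

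The Follow up paragraph just before it makes arrangements for attrition: "When patients drop out of the trial, the reasons for withdrawal will be recorded in detail". It adds that patients lost to follow-up will be contacted again. The protocol gives no dropout rate, no inflation of the sample size and no replacement of lost patients.

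**The concern.** The figure from the power calculation is the number analysed. Here it is also the number enrolled and the number that the protocol says must finish follow-up. These three agree only if all 40 patients provide 6-week data. A plan that writes procedures for withdrawal and loss, but makes its power conditional on there being none, sets a condition that it has no means of protecting.

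What is at stake is the accuracy of the stated power. Readers will take 0.95 as what the trial delivers, and after any loss the protocol's own sentence says that power is not adequate.

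**Working it through.** **Inputs.** From Sample size consideration: d = 0.8, one-sided alpha 0.20, target power 0.95, 1:1 allocation, 20 per group. From Statistical analysis: two-sided significance level 0.05. Loss rates of 5% to 20% are assumptions.

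**Formula.** Exact power of the two-sample t test:
- noncentrality δ = d × √(n1·n2/(n1+n2)), with df = n1 + n2 − 2
- one-sided power = P(T > t_crit), where T is noncentral t with parameters df and δ and t_crit is the 1 − α quantile of the central t
- for two-sided 0.05, t_crit is the 0.975 quantile and the lower tail is added.

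**The plan's own figure.** With 20/20, δ = 0.8 × √(400/40) = 2.5298, df = 38, t_crit = 0.8512 and power = 0.9532. This matches the protocol's output, and 20 is the smallest group size that reaches 0.95.

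**Power after losses.**

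| Analysed | δ | df | t_crit (one-sided 0.20) | Power, one-sided 0.20 | Power, two-sided 0.05 |
|---|---|---|---|---|---|
| 20/20 | 2.5298 | 38 | 0.8512 | 0.9532 | 0.693 |
| 20/19 (one loss) | 2.4972 | 37 | 0.8514 | 0.9499 | 0.682 |
| 18/18 (10% loss) | 2.4000 | 34 | 0.8523 | 0.9389 | 0.645 |
| 16/16 (20% loss) | 2.2627 | 30 | 0.8538 | 0.9204 | 0.591 |

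**Separating the two effects.**
- Attrition on the plan's own inputs: 0.9532 − 0.9389 = 0.014 at 10% loss, and 0.9532 − 0.9204 = 0.033 at 20%.
- Change of significance level with no loss at all: 0.953 − 0.693 = 0.260.
- Attrition at two-sided 0.05: 0.693 − 0.645 = 0.048 at 10% loss, and 0.693 − 0.591 = 0.102 at 20%.

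**Chance that the condition is met.** If losses are independent with probability p, all 40 complete with probability (1 − p)^40. This is 0.129 at p = 0.05, 0.015 at p = 0.10 and 0.0001 at p = 0.20.

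**Would inflating enrolment help?** To keep 20 completers per group, enrol 20/(1 − p), rounded up: 22, 23, 24 or 25 per group at 5%, 10%, 15% or 20% loss. That would protect only a target built on one-sided 0.20. At two-sided 0.05, power of 0.95 needs 42 analysed per group (0.952).

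**The case against.** The strongest reply is that the consequence is small. On the plan's own inputs one loss takes power from 0.9532 to 0.9499, which still rounds to 0.95, and an assumed 20% loss leaves 0.920. This stands: the condition fails with the first loss, but the power barely moves.

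It can also be said that procedures for dropout are not a forecast of dropout, and that contacting lost patients again may keep loss low. Both are fair. The protocol predicts no rate, so every rate used here is assumed. Re-contact helps retention, but it does not create a margin.

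Two stronger readings are tempting and are not supported.
- A reader might infer that attrition is what brings power down to 69% or less. It is not. The 0.693 arises with all 40 patients, because the size was computed at one-sided 0.20 and the analysis uses two-sided 0.05. That mismatch is a separate point.
- A reader might infer that the plan prescribes a completers analysis, from the completion wording together with repeated measures ANOVA. The sentence concerns follow-up, not therapy sessions, and it belongs to a power statement. The Statistical analysis section defines no analysis set, and it also names between-group comparisons at 6 weeks that can use anyone with a 6-week value. Analysis sets and missing-data rules are commonly left to the SAP, which is not at hand.

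**Conclusion.** The inconsistency is real and is fixed in the protocol itself: the required completers equal the enrolled patients, with no margin or replacement. The stated completer number, and strictly the 0.95 power, hold only with zero loss.

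The size is modest on the plan's own inputs, about 1.4 points of power at 10% loss and 3.3 points at 20%. At the significance level that the analysis uses, the same losses cost about 4.8 and 10.2 points, from a starting value of 0.693. These figures assume d = 0.8, equal loss in the two groups and a simple comparison of two means at 6 weeks. The loss rates are illustrative.

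The sentence needs correcting because it states a power that the design cannot guarantee. The sample size arithmetic itself reproduces.

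**What to change.** In the Power analysis paragraph, remove the condition that 20 per group must complete, and state power at the number expected to provide 6-week data. Compute it at the level the analysis uses and mark the loss rate as an assumption. Possible wording: *Forty patients (20 per group) will be enrolled. For d = 0.8 at two-sided 0.05, power is 0.693 if all provide 6-week data, 0.645 with 18 per group (assumed 10% loss) and 0.591 with 16 per group (assumed 20% loss).*

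The preceding sentence of that paragraph, which gives power as 0.95, has to change with it, or the paragraph will contradict itself.

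No added enrolment is needed for this correction. The cost is a change of wording and a less favourable stated power. Adding a dropout allowance to 20 per group would not be a substitute, because it leaves the alpha mismatch in place.
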